### Statistics methods

#### Power and sample size

For this RCT, we define the clinically significant change in DBI as 0.5, the equivalent of one medication contributing to DBI given at the minimal efficacious dose [14]. Approximately 4% of recent interRAI assessments show a ΔDBI ≥ 0.5 over 6 months. Therefore, a meaningful outcome from deprescribing in this study would be to increase the percentage, in the intervention cohort, with a DBI change ≥of 0.5 by 10% points. This would bring the percentage ΔDBI ≥ 0.5 over a 6-month period to 14%.

The null hypothesis is that there is no difference in proportions with a ΔDBI of ≥ 0.5 over 6 months between the control and intervention groups, given that 4% of participants in the control group have a ΔDBI of ≥0.5. Therefore, to disprove the null hypothesis, we need to detect a change in the number of participants of 10% or more with a ΔDBI of ≥0.5 with a power of 90% at an *α*=0.05. This requires 167 participants in each arm of the study, 334 in total.

For each frailty stratum under the null hypothesis, there will be no difference in change in DBI between the control and intervention groups and assume 4% of participants in the control group have a reduction in DBI of ≥0.5, then to detect a change in the number of participants of 20% or more with a reduction in DBI of ≥0.5 with a power of 80%, and at *α*=0.017 (0.05/3), requires 56 participants in each arm of the study (112 in each stratum, 336 in all).

It is estimated that over 12 months within the target areas of the district health boards’ approximately 650 participants will meet the basic inclusion criteria, including the minimum DBI. In addition, previous data suggest that approximately 50% of the study’s cohort will take the target medicines, and therefore, 325 people would be eligible to take part in the study per annum.

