## Background

Polypharmacy, the use of five or more of medications, is prevalent amongst older adults positioning them at a higher risk of drug-drug interactions and one or more inappropriate medications. Inappropriate medications are defined as those whose potential harm outweighs their possible benefits currently in the individual [1]. Deprescribing, the process of safely reducing or discontinuing unnecessary or harmful medicines with clinical supervision, can decrease polypharmacy, reduce inappropriate medicine use, and may improve health outcomes [2].

Disease-specific guidelines offer little advice regarding deprescribing potentially harmful medications [3, 4] for people with multimorbidity. Of note, anticholinergic and sedative medications can be inappropriately prescribed for older adults [5]. The cumulative, long-term use of these medications is associated with several negative health consequences, including impaired muscle strength, worsening cognition, increased frailty, poorer physical functioning (e.g., balance), heightened risk of falls, increased rate of hospitalizations, entry into residential care, and even death [6, 7]. Polypharmacy is associated with frailty [8], a geriatric syndrome present in many older adults. Frailty increases with age due to age-related physiological deterioration. Up to half of the people aged over 85 years experience frailty [2]. Small trigger events, like a seasonal illness or fall, can cause a sudden decline in health and negative outcomes in already frail individuals [2, 9, 10]. Little is known on how a quantified measure of frailty could inform and help in targeting frail individuals for deprescribing.

Deprescribing of unnecessary anticholinergic and sedative medications has been shown to potentially improve health outcomes of older people [2, 9], including cognition [10], and reducing the risk of falls [11] and hip fractures. In addition, although inconclusive to date, evidence suggests that deprescribing could improve reported quality of life [12, 13].

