### Participants

Participants will be eligible for inclusion if they are as follows:
Are aged ≥65 yearsHave undergone an interRAI Home Care [24] or contact [25] assessmentAre regularly taking at least one anticholinergic or sedative medication as shown in the interRAI or dispensing records.

Participants will be excluded from the study for any of the following reasons:
Not consenting for their interRAI data to be used for researchHaving a psychiatric disorder or dementia disease (e.g., Alzheimer’s disease, dementia, schizophrenia, abnormal thought processes, delusions, hallucinations)Scoring 3 or higher on the interRAI Cognitive Performance ScaleHaving a terminal illness with life expectancy ≤6 monthsDetermined as non-frail by having no deficits in the frailty indexHaving an initial DBI score of <0.5 (DBI score of 0.5 is the equivalent of one DBI medication being taken at the minimum efficacious dose) [14].Having a potentially life-threatening drug interaction requiring urgent medical intervention (during the study period)

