#### Intervention arm

In the intervention arm of the trial, pharmacists will discuss with participants the medical conditions with which the DBI medications have been prescribed and their experiences with these medications. The consultation will determine if the potential harm of DBI medications prescribed outweigh their possible benefits. The participant and their family’s beliefs about the continued need for these medications and their preferences regarding willingness to discontinue these medications will also be determined via the consultation. After the consultation, target anticholinergic/sedative medications will be documented along with the participant’s concerns regarding these medications. Study pharmacists will consider the participants’ medical history as conveyed by the participants, their interRAI assessments, and their electronic medication records, if available.

The deprescribing implementation strategy that will be employed will focus on reducing or stopping anticholinergic and sedative medications to reduce participants’ DBI scores, using a process that was adapted from [2] and previously trialled in a New Zealand residential aged care setting [28, 29]. The process used in this study will differ from that used in the above residential care study because our study pharmacists will not have access to prescribing lists and clinical records before meeting the participants. Nevertheless, face to face consultations with the study pharmacists will capture rich data on participants’ medical history, medication lists, and their beliefs about their medications.

The deprescribing medication review will involve the following:
Pharmacist review of medication useParticipant consultationPharmacists suggesting changes in DBI medications to GPsGP consultation with the participantsGP decision to revise or not to revise DBI medication prescriptions

All medication reviews and DBI calculations will be reviewed and verified independently by a senior pharmacist (author [name]). All suggestions developed on potential deprescribing will be peer-reviewed by another study pharmacist before sending them to the participant’s GP, with additional expertise being available from the senior pharmacist.

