#### Primary outcome

The primary outcome will be the change in a participant’s DBI (ΔDBI) between the time of the baseline interRAI assessment (T1) and the time of 6 months of follow-up (T2; ΔDBI = DBI_T1_ – DBI_T2_). Data for the calculation will be collected by comparing medication use pre-and post-intervention. We will determine if there is a greater reduction in the DBI of participants in the experimental arm of the trial compared with participants with the same level of frailty in the control arm. Subgroup analysis will determine if deprescribing is more pronounced for those with more severe frailty.

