#### Secondary outcomes

Secondary outcomes measures will be compared between the two arms of the trial after 6 months and are outlined in Table 3. From the funder’s perspective, these include the number of hospitalizations, emergency department visits, entry into aged residential care, all-cause mortality, and cost-utility. In addition, we will measure the number of emergency department visits and unplanned hospital admissions. Data on entry into or change in the level of care in aged residential care will be extracted from relevant national databases by the analytical services of the Ministry of Health. Patient mortality data will be matched using participants’ National Health Index (NHI) number, added to the dataset, and analyzed using competing risk regression. In a separate analysis, we will conduct a health cost utility assessment.

**Table 3 Tab3:** Outcome measures and analysis

Outcome	Measure	Alternative hypothesis	Analysis
Drug burden change	Proportion ΔDBI ≥ 0.5	Intervention greater	*χ*^2^ comparison of proportions
Emergency department visits	Proportion	Remain the same or decrease	*χ*^2^ comparison of proportions
Unplanned hospital admissions	Proportion	Remain the same or decrease	*χ*^2^ comparison of proportions
Admissions into aged residential care	HR	Remain the same or decrease	CRRA
Mortality	HR	Remain the same or decrease	CRRA

*ΔDBI* change in Drug Burden Index, *WSR* Wilcoxon signed-rank test, *CRRA* competing risk regression analyses, *χ*^2^ chi-square

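### The primary outcome is change in DBI and dose reduction counts as deprescribing, but the only DBI analysis named scores every fall below 0.5 as no response

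*Protocol article*

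**What the plan says.** **What counts as deprescribing.** The Background section defines it as "the process of safely reducing or discontinuing unnecessary or harmful medicines with clinical supervision". The Intervention arm section describes the strategy as "reducing or stopping anticholinergic and sedative medications to reduce participants’ DBI scores". Lowering a dose and stopping a medicine both count.

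**The primary outcome.** The Primary outcome section begins "The primary outcome will be the change in a participant’s DBI (ΔDBI", computes ΔDBI as the T1 value minus the T2 value, and asks whether DBI falls more in the experimental arm. It sets no cut, and neither does the Abstract.

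**What is tested.** The DBI row of Table 3 gives the measure as "Proportion ΔDBI ≥ 0.5", compared by chi-squared. The Power and sample size section states its null hypothesis on that proportion, and the Statistical analysis section names only the chi-squared comparison of proportions for such measures. The Table 3 footnote and the abbreviation list expand WSR as the Wilcoxon signed-rank test, but no row uses it.

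**The meaning of 0.5.** The Power and sample size section says "we define the clinically significant change in DBI as 0.5, the equivalent of one medication contributing to DBI given at the minimal efficacious dose". The Participants section excludes an initial DBI below 0.5 and explains that a "DBI score of 0.5 is the equivalent of one DBI medication being taken at the minimum efficacious dose".

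**The concern.** The outcome definition, the intervention and the named test do not measure the same thing. The outcome is a continuous change, and the intervention can act by lowering doses. The test sees only falls as large as one medicine at the minimum efficacious dose.

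The primary objective is whether pharmacist reviews lead GPs to deprescribe. If some GPs respond by lowering doses, part of that response may fall under the cut and be counted with participants whose prescriptions did not change. With no other DBI comparison named, a null result could be reported as absence of deprescribing when doses had in fact been lowered.

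**Working it through.** **1. The plan's own figure.** Inputs from the Power and sample size section: 4% in control, 14% in intervention, α = 0.05 (taken as two-sided), 90% power. The 1:1 ratio is in the Study design section. With unpooled variance:

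n = (1.960 + 1.282)² × (0.04 × 0.96 + 0.14 × 0.86) / 0.10² = 10.507 × 0.1588 / 0.01 = 166.9, so 167 per arm.

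This is the stated number. The pooled-variance formula gives 171. Power at 167 per arm with the pooled test is 89.5%.

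**2. The entry floor, from the document alone.** One medicine at the minimum efficacious dose gives DBI = 0.5. If some of it remains in use, its remaining score is above 0, so ΔDBI = 0.5 − (something above 0) < 0.5. Only a complete stop reaches the cut.

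**3. Higher doses, under two assumed forms.** The article calls the DBI linear and additive but gives no per-medicine formula. Let k be the dose as a multiple of the minimum efficacious dose. Both forms below give 0.5 at k = 1.

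*Form A, saturating:* score = k/(k + 1). Halving one medicine gives k/(k + 1) − k/(k + 2).

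*Form B, proportional:* score = 0.5k. Halving gives 0.25k.

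| Starting dose (k) | ΔDBI from halving, A | ΔDBI from halving, B | Reaches 0.5? |
|---|---|---|---|
| 1 | 0.167 | 0.25 | neither |
| 1.5 | 0.171 | 0.375 | neither |
| 2 | 0.167 | 0.50 | B only |
| 3 | 0.150 | 0.75 | B only |
| 4 | 0.133 | 1.00 | B only |

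Under A the largest drop from halving is 0.172 (at k = √2), and the largest from a 75% cut is 0.333 (at k = 2). A reduction to the minimum dose gives k/(k + 1) − 0.5, which is always below 0.5. Because scores add across medicines, three halvings near the maximum would reach the cut (3 × 0.172 = 0.516) and two would not (0.344). Under B, halving a single medicine counts from k = 2 upward.

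Both forms miss some dose reductions, and they differ widely in how many.

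**4. What cannot be computed.** The article gives no dose distribution, no expected split between stops and reductions, and no mean or standard deviation of ΔDBI. Neither the share of reductions missed nor the power of a continuous analysis can be derived from it.

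**The case against.** The strongest reply is that 0.5 is a deliberate, referenced threshold of clinical relevance. Scoring smaller falls as non-response is what a responder threshold does, and the null hypothesis, sample size and Table 3 use it consistently. This stands as a reason to keep the cut. It does not explain why the cut is the only DBI comparison named when the outcome is defined as the change itself.

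A second reply is that smaller falls are not outside the protocol: the outcome is stated without a cut, and the Data entry and quality checks section prepares the data for medication-specific analyses. The full analysis plan is not shown and may hold more. But that section describes no between-arm comparison, and Table 3 does fix a measure and a test for DBI.

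Three stronger readings are tempting, and the document supports none of them.

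- *That the cut misses most dose reductions.* This follows under form A but not under form B, and reductions across several medicines add up. The case that needs no formula is one medicine at the entry floor, and the article does not say how many participants that covers.
- *That the 90% power is overstated.* One could treat the 10 points as uptake of any kind and suppose that a quarter, half or three quarters falls below 0.5. The comparison becomes 4% v 11.5%, 9% or 6.5%, with power 73%, 46% or 17%. But the Power and sample size section defines the 10 points as an increase in the percentage at or above 0.5, however reached, so there is nothing to discount.
- *That an any-reduction measure would have more power.* Keep a 10-point difference and assume a 4% background of smaller reductions in both arms: 8% v 18% gives about 78%. At backgrounds of 8%, 10%, 15% and 20%, power is 68%, 65%, 57% and 52%. If a quarter of uptake lies below the cut, the existing test's 73% is already better from 8% background upward. No general gain can be claimed.

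**Conclusion.** The point holds as a mismatch between the outcome and its analysis, with some loss of sensitivity. The trial defines its outcome as change in DBI and its intervention as reducing or stopping, yet the one DBI test named cannot register a fall below 0.5. From the document alone, this covers every dose reduction short of stopping for a participant on one medicine at the minimum efficacious dose. Beyond that, its extent depends on the assumed form: under A, no halving of a single medicine counts; under B, only those from twice the minimum dose upward do.

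The threshold is legitimate, and the stated sample size and power stand for the test they were built for. This is a cheap improvement that lets the trial answer its stated question. It is not a design error.

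**What to change.** 1. Keep the ΔDBI ≥ 0.5 row as the sized test and describe it as a reduction equivalent to one medicine at the minimum efficacious dose.
2. Add to Table 3 a between-arm analysis of ΔDBI as a continuous variable, adjusted for baseline DBI and frailty stratum, reported as a difference in mean change with its 95% confidence interval. This matches the Primary outcome section directly.
3. Add a supporting row for the proportion with any net reduction or stop of a Table 1 medicine between T1 and T2, showing stopped and reduced separately.
4. State that a null result on the 0.5 cut alone will not be read as no deprescribing.

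The sample size text needs no change.

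**Cost.** Table rows and wording only. The daily dose of every medicine is recorded at baseline and again at follow-up by the same process, so no extra participants, visits or data are needed. There are two downsides. The continuous analysis must be given a place in the testing order before unblinding, for example after the sized comparison. The any-reduction row is sensitive to recording noise, so it should support the 0.5 cut and not replace it.

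### The 4% control rate is quoted for interRAI assessments with no stated DBI restriction, yet the trial enrols only people with DBI of at least 0.5; if the 4% is unrestricted, the eligible control rate is higher and power at 167 per arm is below 90%

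*Protocol article*

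**What the plan says.** All references are to the protocol article.

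- **Source of the rate** (Power and sample size): "Approximately 4% of recent interRAI assessments show a ΔDBI ≥ 0.5 over 6 months". No restriction on the records is stated.
- **Use of the rate** (same section): the null hypothesis is framed "given that 4% of participants in the control group have a ΔDBI of ≥0.5".
- **Target effect** (same section): the aim is to raise the share of the intervention group "with a DBI change ≥of 0.5 by 10% points", that is, to 14%. With 90% power and alpha 0.05, "This requires 167 participants in each arm of the study, 334 in total".
- **Strata** (same section): the same 4% is used for each frailty stratum, there worded as a reduction, with a 20% change to detect, 80% power and alpha 0.017 (0.05/3). This gives 56 per arm.
- **Eligibility** (Participants): regular use of at least one anticholinergic or sedative medicine is required, and an initial DBI below 0.5 is an exclusion.
- **Outcome** (Primary outcome): ΔDBI is the T1 value minus the T2 value, so a positive value is a reduction.
- **Recruitment** (Power and sample size): about 650 people a year are expected to meet the basic criteria, the minimum DBI included. The text then halves this because about 50% of the cohort "will take the target medicines, and therefore, 325 people would be eligible to take part in the study per annum".

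**The concern.** The control rate and the trial population do not appear to match. DBI cannot fall below zero, so a person who starts under 0.5 can never have a reduction of 0.5. In an unrestricted set of assessments such people count in the denominator and never in the numerator. The trial removes all of them, so the rate among those left must be higher than in the whole set, other things equal.

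This matters because the target is an absolute difference of 10 points. At rates this low, the variance of a proportion rises steeply with the rate, so the same 10 points are harder to detect from a higher base. The 4% is the only empirical input to both the overall and the per-stratum calculation, so both are affected.

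The recruitment sentence raises a related doubt. Anyone who meets the minimum DBI already takes a target medicine, so halving that group for medicine use applies the same condition twice. It leaves unclear to which population the section's figures refer.

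**Working it through.** **Inputs from the article:** control rate 4%; difference 10 points; 167 per arm; 1:1 allocation; alpha 0.05 (sidedness not stated; the two-sided value reproduces the plan); chi-squared test. Per stratum: 56 per arm, alpha 0.05/3, and the 20% change read as 20 points (4% versus 24%).

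**1. The plan's own figure.** Two proportions, unpooled variance, two-sided, no continuity correction:

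n = (1.960 + 1.2816)² × (0.04×0.96 + 0.14×0.86) / 0.10² = 10.507 × 0.1588 / 0.01 = 166.9, so 167 per arm.

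This matches exactly. The pooled-variance formula gives 171, and 89.5% power at 167.

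**2. Effect of the entry criterion on the rate.** Let f be the share of source records with DBI of at least 0.5. All reductions of 0.5 or more come from that share, so the rate within it is 4%/f. The article does not give f. As assumed values:

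| Assumed f | 4%/f |
|---|---|
| 1.0 | 4% |
| 0.8 | 5% |
| 0.5 | 8% |
| 0.4 | 10% |

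**3. Power at 167 per arm, 10-point difference held.** Unpooled: power = Φ(0.10 / √(V/167) − 1.960), with V = p(1−p) + (p+0.10)(0.90−p).

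| Control rate p | V | Unpooled power | Pooled power |
|---|---|---|---|
| 4% | 0.1588 | 90.0% | 89.5% |
| 5% | 0.1750 | 87.1% | 86.5% |
| 6% | 0.1908 | 84.1% | 83.5% |
| 8% | 0.2212 | 78.5% | 77.8% |
| 10% | 0.2500 | 73.4% | 72.7% |
| 12% | 0.2772 | 69.0% | 68.3% |

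For scale, 90% power at 8% versus 18% would need 10.507 × 0.2212 / 0.01 = 232.4, so 233 per arm (236 pooled).

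**4. Per stratum, 56 per arm, 20-point difference, alpha 0.05/3 (critical value 2.394).**

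| Control rate | Unpooled power | Pooled power |
|---|---|---|
| 4% | 78.6% | 75.3% |
| 8% | 67.7% | 64.6% |
| 10% | 63.2% | 60.3% |

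At 4% the figure is already a little under the stated 80% (the unpooled formula asks for 58 per arm, the pooled one for 62). That small gap comes from the formula, not from the control rate. The fall from the 4% row to the 8% row, about 11 points by either formula, is the part due to the control rate.

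**5. Recruitment.** 650 × 0.50 = 325. The 650 already includes the minimum DBI, and a DBI of 0.5 or more requires at least one DBI medicine, so the factor 0.50 has no group left to remove.

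**The case against.** A reader might infer that the 4% is known to be understated and that 90% power is therefore not delivered. The document does not support that. It does not say which records the 4% was computed on, and they may already have been limited to users of these medicines or to DBI of at least 0.5. How a planning rate was derived is often left to the full protocol, which is not shown. This stands: the loss of power is conditional.

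Nor is 8% an estimate. It would follow from 4%/0.50, but the 50% is given as a share of the study's cohort, directly after a count that already includes the minimum DBI. It is not a share of the records behind the 4%, so 8% is one illustration within a range.

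Three further points limit the claim:

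- **Direction of change.** The overall paragraph speaks of a DBI change. If the source counted rises as well as falls, its rate of reductions is below 4%, which would offset the bias. The definition of ΔDBI and the wording for the strata point to reductions, but the source's own definition is not given.
- **Other exclusions.** Removing people with dementia or psychiatric disorder could move the rate either way.
- **Absolute or relative effect.** The loss depends on holding 10 points. If the 3.5-fold ratio (14%/4%) held instead, 8% versus 28% would give over 99% power. The article, however, fixes the meaningful effect in percentage points.

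The recruitment figure enters neither sample size, so its error does not itself show that power is lost. Nor is 167 an arithmetic mistake.

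**Conclusion.** The point holds in conditional form. The article applies to its control arm a rate quoted for interRAI assessments without a DBI restriction, while its eligibility rules remove everyone who could not reach the outcome. If the source is unrestricted, as the wording reads, and the 4% counts reductions, the eligible control rate exceeds 4%, apart from any effect of the other exclusions. With 10 points held at 167 per arm, power is then about 87% to 69% for control rates of 5% to 12%, against the stated 90%. Per stratum, power is about 75–79% at 4% and 65–68% at 8%, against the stated 80%. The document does not settle where in this range the trial lies. The double use of medicine intake in the recruitment estimate is an inconsistency whatever the source of the 4%.

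**What to change.** - Recompute the 6-month rate of a reduction of at least 0.5 in interRAI records that meet the trial's own criteria, including an initial DBI of at least 0.5, and use it in place of 4%. If the 4% was already so restricted, state that. Say in either case that only reductions are counted.
- Restate overall and per-stratum power at the planned size over a range of control rates, for example 4% to 12%, and name the formula.
- Correct the 650/325 sentence so that medicine use is not applied again to people who already meet the minimum DBI.

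The cost is one new query of the assessment data and some restated figures. The stated power is likely to look less favourable. No extra patients are needed.
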